**Recruitment**

**Consent, Baseline Blood Sample**

10ml blood

**Dietary Assessment 1**

**Blood**

Genotype for GST family (10ml)

**Sample Collection 1**

Up to 6 prostatic biopsies

**Biopsy**

RNA expression (up to 6 cores)

**Intervention Period 1**

Distribution of broccoli and peas to volunteers

Compliance phone calls

**Urine**

ITCs and metabolites

1x24 hour collection

**Sample Collection 2**

Up to 6 prostatic biopsies

5ml blood

1x24 hour urine collection

**Intervention Period 2**

Distribution of broccoli and peas to volunteers

Compliance phone calls

**Sample Collection 3**

Up to 6 prostatic biopsies

5ml blood

**SAMPLING**

**Blood**

PSA (5ml)

**Biopsy**

RNA expression (up to 6 cores)

**Biopsy**

RNA expression (up to 6 cores)

**Blood**

PSA (5ml)

**STUDY DESIGN**

**Dietary Assessment 2**

**Dietary Assessment 3**

**Information Exchange**

**Blood**

PSA (5ml)

*Figure 2 Plan of sample collection*

**Dietary Intervention**

After giving fully informed, written consent, the volunteers will be matched by genotype and cruciferous vegetable consumption. The diet diary will be used to define high (> 3 portions per week) or low (< 1 portion a week) habitual consumers of cruciferous vegetables. Volunteers will be divided into two dietary intervention groups accordingly.

1. The ‘peas’ group will be asked to consume an additional 4 portions (100g each) of peas per week as part of their normal diet.

2. The ‘broccoli’ group will be asked to consume an additional 4 portions (100g each) of a special variety of broccoli, selectively grown for its enhanced glucosinolate content, per week as part of their normal diet.

Volunteers will be asked to modify their diets for a total of 12 months. This is to enable us to detect any long-term changes in gene expression and to coincide with the routine TRUS examinations every 6 months. Volunteers can choose which day to eat the vegetables, but will be asked to keep a record of when the vegetables were eaten.

Should the volunteers wish to go on holiday during the 12-month period, they will not be expected to adhere to the intervention. We will ask the volunteers to inform us of their planned holiday dates so that we can keep a record. We will ask them to avoid booking holidays for more than four weeks at a time or two weeks either side of their visits to the clinic and not within a month of the final assessment.

*Supply of Vegetables*

The broccoli will be grown and harvested by Olga Ltd, Boston, Lincolnshire, and processed by Christian Salvesen, Bourne, Lincolnshire. The broccoli is a hybrid cultivar, conventionally crossed with a wild species that has an enhanced level of the glucosinolate called glucoraphanin (precursor of sulforaphane). Samples will be packaged into 100g portions and stored frozen at -18oC until cooked by the volunteer. Frozen peas will be bought from a supermarket. Both types of frozen vegetable will be delivered to the volunteers on a regular basis by a member of the study team or Polymek, a temperature controlled delivery service, at a time convenient to the volunteer. Should any volunteer not own a freezer, IFR will loan a PAT tested freezer to the volunteer for the duration of the study.

*Cooking Guidelines for Frozen Vegetables*

Volunteers will be provided with a steamer and given a demonstration of how to cook the vegetables by the Diet Cooks at HNU. Portions of broccoli will be steamed for 4-5 minutes and portions of peas will be steamed for 2-3 minutes. It is important that volunteers do not over cook the broccoli as this will result in delayed absorption of isothiocyanates produced. Previous studies conducted at IFR have demonstrated cooking levels required to maximize the level of ITCs ingested (unpublished data). Levels of glucosinolate and the equivalent isothiocyanates in the enriched broccoli hybrid have been measured previously at IFR, Mithen *et al* (2003). The levels correspond to a 3-4 fold increase compared to standard supermarket broccoli.

**SAMPLE ANALYSIS**

*Blood Samples*

A 10ml sample of blood will be taken from which genomic DNA will be extracted using the QIAamp DNA Mini kit protocol (Qiagen Inc). Samples will be doubly encrypted to protect the volunteer’s identity. DNA samples extracted from whole blood will be amplified using real-time PCR using the method of Cotton *et al* (2000), to determine the presence or absence of GSTM1 and GSTT1 genotypes. The frequency of variant alleles for GSTPi will also be determined. A 5ml sample of blood will be collected at baseline and at each visit to the urology clinic. This will be tested for the level of PSA, a protein that the prostate produces. PSA level will be determined by the Biochemistry department at the NNUH.

*Urine Samples*

Total volume of urine collected during 0-24 hours post broccoli consumption will be recorded and sub samples of 20ml will be stored at –20°C until analysis. The remaining urine will be discarded. A validated liquid chromatography-tandem electrospray ionisation mass spectrometry method will be used to measure the concentrations of the following ITCs in urine samples: Iberin and sulforaphane and their glutathione, cysteine-glycine, cysteine and N-acetyl cysteine conjugates. Quantification by internal standardisation, using authentic calibration standards for each analyte, such that is standard practice in our laboratory will also be used (method in publication).

*Biopsy Samples*

*Biopsies 1-6 Hybridised onto Affymetrix Microarrays*

Two from the first sample collection day, two from the second sample collection day and two from the third sample collection day, one from each lobe.

*Biopsies 7-12 – Confirmation of Expression by RT-PCR*

Two from the first sample collection day, two from the second sample collection day and two from the third sample collection day, one from each lobe.

Biopsies will be placed in RNA later and snap frozen in liquid nitrogen. Total RNA will be extracted directly from the prostate biopsies following snap freezing in RNALater™ (Ambion). This product ‘freezes’ gene transcription and stabilises the RNA present so that it can be extracted at a later stage. Total RNA isolation will be performed using RNeasy kits (Qiagen) according the manufacturer’s instructions; these are used routinely for the extraction and purification of RNA. Preliminary investigation has demonstrated that sufficient RNA of high quality can be obtained from a single needle biopsy sample.

The RNA extracted from the biopsy samples will be concentrated and the quality assessed using Agilent technologies lab-on-a-chip RNA 6000 nano assay. RNA of sufficient quality will be hybridised onto human Affymetrix U133Plus 2.0 probe arrays at the School of Biosciences, University of Nottingham. The arrays carry >47,000 transcripts, expression profiling will be performed for each transcript and the data produced will be analysed using market-leading software. Gene transcript levels in each test sample will be normalised against the values for the standard. We are particularly interested in the expression of genes that are known to respond to treatment with ITCs *in vitro* and/or in animal models.

*TaqMan Real-Time RT-PCR Assay*

Target gene mRNA levels will be determined by real-time RT-PCR using the ABI prism 7700 Sequence Detection System (Applied Biosystems, Foster City, CA). The threshold cycle (Ct) is defined as when the fluorescence signal reaches ten-times the noise signal level (baseline). Forward and reverse primers, and the fluorogenic TaqMan probes for target genes, will be designed using Primer Express Software (Applied Biosystems). Sequence homology of selected oligomers will be checked using a National Center for Biotechnology Information BLAST search to ensure that sequences will be specific to target genes. Primer and probe sets will be obtained from Sigma-Genosys, The Woodlands, TX and Applied Biosystems, respectively.

A number of TaqMan assays have already been developed and validated at IFR, and some of these are for genes that have been shown (by IFR and others) to respond *in vitro* to treatment with SFN at the level of transcription. These genes include: Thioredoxin reductases (*TR1* and *TR*2), quinone reductase (*QR*1), glutathione-S-transferase A1 (*GSTA1*), UDP-glucuronosyltransferase (*UGT1A1*), cyclooxygenase-2 (*COX2*), multidrug resistance protein-2 (*MRP-2*), Nuclear Factor Kappa B *(NF-B)* and Kruppel-like Factor 4 *(KLF4).*

**STATISTICAL ANALYSIS**

*Statistical Power*

It is not possible to calculate the power for differences in gene expression between the two intervention groups because to date there are no relevant publications that describe the effects of ITCs on gene expression *in vivo*. This is a pilot study designed to provide data from which to calculate power for future studies in this field. The nature of a power calculation is to obtain the probability of detecting a difference that is true as opposed to a false negative result. It is arguable as to the appropriateness of such calculations when applied to Affymetrix gene expression data because the number of genes is so large (>47,000). Therefore we are more concerned with controlling false positive results (type I error).

All array data will be analysed using a simple linear model comparing significant differences in gene expression between broccoli and pea treatment groups. Impact of genotype will also be included, combining regression analysis with analysis of group differences. Pair wise comparisons between time points (baseline, mid and end points) and treatment (broccoli or peas) will be made by dividing by signal intensity to give a fold induction for each gene. Advice will be sought from [name], Biostatistician at the Institute of Food Research, Norwich.

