Prostate biopsy tissue will be taken before and after intervention of either broccoli or peas. We are primarily interested in the effect of broccoli on gene expression. However, peas are a good control because they cause the same change to the volunteers’ dietary regimen as adding broccoli and because they contain negligible amounts of glucosinolates. There is epidemiological evidence that peas may also be beneficial in reducing prostate cancer risk, but by different pathways to SF mediated action, Key *et al* (1997).

The study will use changes in gene expression as the main biomarker of effect. RNA will be extracted from the tissue and hybridised onto Affymetrix arrays. We will use validated software to create a gene expression profile of functional clusters of genes that are perturbed by the broccoli intervention. Subsequent analysis of selected genes by RT-PCR will confirm any significant changes in gene expression.

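### The protocol puts control of false positives first, but the analysis it describes for more than 47,000 transcripts controls no error rate, and RT-PCR in the same men is not independent replication

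*Protocol*

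**What the plan says.** The Statistical Analysis section first explains why there is no power calculation: "It is not possible to calculate the power for differences in gene expression between the two intervention groups". It cites the lack of published in vivo data and the pilot status of the study. It then doubts the value of power calculations for so many genes and concludes: "Therefore we are more concerned with controlling false positive results (type I error".

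The next paragraph sets out the analysis. The main step is this: "All array data will be analysed using a simple linear model comparing significant differences in gene expression between broccoli and pea treatment groups". Genotype is added to the model. Then: "Pair wise comparisons between time points (baseline, mid and end points) and treatment (broccoli or peas) will be made", obtained by dividing signal intensities to give a fold induction per gene. A biostatistician's advice is to be sought.

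The Sample Analysis section gives the scale: "The arrays carry >47,000 transcripts, expression profiling will be performed for each transcript". It expresses particular interest in genes known to respond to isothiocyanates (ITCs) and gives examples with existing assays, but does not make them a separate test family.

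On follow-up of array results, the Background says: "Subsequent analysis of selected genes by RT-PCR will confirm any significant changes in gene expression". Under Biopsy Samples, cores 1-6 go to the arrays and cores 7-12 to RT-PCR. Each set has two cores from each of the three collection days, one per lobe.

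**The concern.** The stated priority and the stated analysis do not match. None of the three elements (linear model, genotype effects, fold inductions) limits the number of false positives across tens of thousands of transcripts. A fold ratio taken alone has no error rate.

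That leaves RT-PCR as the only described check on the array findings. It measures the same men again at the same visits. If the men in one arm happen to differ from those in the other on some transcript, their second cores will tend to show the difference too. Agreement between the two assays would then be read as confirmation of a dietary effect when it shows only that the measurement was repeatable.

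Gene expression is the first objective and the main biomarker of effect, and the pilot is meant to supply inputs for powering later studies. Effect sizes taken from unadjusted, selected hits tend to be too large, so studies planned on them would tend to be too small.

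**Working it through.** The protocol states no alpha, error rate or fold cut-off, so there is no figure of its own to reproduce.

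**Inputs**
- Transcripts: m = 47,000, used as a lower bound (Sample Analysis).
- Group size: 20 per arm (Study Design).
- Per-transcript two-sided alpha: not stated; assumed 0.05, 0.01 and 0.001.
- Within-man correlation (rho) between the array value and the RT-PCR value of the quantity compared: not stated; assumed 0 to 0.9.

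**Step 1: expected false positives on one contrast with no true effects.** The formula is m × alpha, which holds however the transcripts are correlated.
- 47,000 × 0.05 = 2,350
- 47,000 × 0.01 = 470
- 47,000 × 0.001 = 47

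The chance of at least one false positive, 1 − (1 − alpha)^m if transcripts are independent, is essentially 1 at all three levels.

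**Step 2: how many also pass RT-PCR in the same men.** Null genes were simulated with 20 men per arm. Each man has an array value and an RT-PCR value with correlation rho. A gene passes if RT-PCR gives p < 0.05 in the same direction as the array. With 200,000 null genes and array alpha 0.05:

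| rho | share passing | of 2,350, if every hit were taken forward |
|---|---|---|
| 0 | 2.6% | 61 |
| 0.3 | 9% | 211 |
| 0.5 | 17 to 18% | 418 |
| 0.7 | 32% | 751 |
| 0.9 | 58% | 1,352 |

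The row rho = 0 corresponds to replication in different men: a null gene passes in the right direction half of 5% of the time, about 2.5%. The excess in the other rows comes from measuring the same men twice.

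A stricter array threshold cuts the count but raises the share that passes, because only the larger chance differences are left. At array alpha 0.001, roughly one in six pass at rho 0.3, over a third at 0.5 and over nine in ten at 0.9.

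Only selected genes go to RT-PCR, so the counts in the last column are upper figures for each rho. The shares apply to null genes selected on array significance alone.

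**The case against.** The strongest reply is that multiplicity methods usually sit in a statistical analysis plan, which is not at hand here. The section does not say that tests will be unadjusted, and it promises biostatistical advice. This has force: a missing method alone would be no finding, and a reader who infers that the protocol decided against adjustment goes too far. What remains is a mismatch within one section, which names type I error as the priority and then describes an analysis without that property.

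Three other strong readings are tempting, and the protocol does not support them.
- *That type I error control is the sole reason for having no power calculation.* The absence of in vivo data comes first, then the pilot purpose. The type I sentence closes a further argument about gene numbers.
- *That RT-PCR cannot remove false positives.* It uses separate cores and a different assay, so it can remove those arising from array noise or core-to-core variation. At modest correlations it removes most of them. The sound statement is that it is not independent replication.
- *That false positives should be summed over every pairwise comparison.* Three time pairs in each of two arms plus three between-arm contrasts would make nine, and 9 × 2,350 = 21,150. But the pairwise comparisons are described as ratios, with no significance test stated, so that total assumes tests the text does not specify.

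It can also be said that a hypothesis-generating pilot tolerates false leads. That lowers the consequence but does not reconcile the priority with the analysis.

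**Conclusion.** The point holds in this form: the protocol ranks control of false positives first, describes an analysis with no error-rate control, and relies on a confirmation step that is not independent of the discovery step. On one contrast with no true effects, between 47 and 2,350 false positives are expected as the assumed alpha runs from 0.001 to 0.05. At array alpha 0.05 and 20 men per arm, about 9%, 17 to 18% and 58% of them would also pass RT-PCR at within-man correlations of 0.3, 0.5 and 0.9.

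Both alpha and the correlation are assumptions, because the protocol gives neither. The figure of 20 per arm is the design number. Fewer analysed men would not change the expected number of array false positives. The plan should be changed on this point, but the pilot status means that the defect does not undermine the study as a whole.

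**What to change.** In the Statistical Analysis section:
- Declare one primary contrast: the between-arm difference in change from baseline to month 12.
- Apply a Benjamini-Hochberg false discovery rate, for example 5%, across all transcripts on that contrast.
- Label all other contrasts, genotype effects and fold inductions exploratory.

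In the Background and under Biopsy Samples, describe RT-PCR of array-selected genes as technical validation of the measurement, not as confirmation of an effect.

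Optionally, pre-specify the named ITC-responsive genes with existing TaqMan assays as a small separate family, measured in every man whatever the array shows, with Holm adjustment. The protocol already notes: "A number of TaqMan assays have already been developed and validated at IFR". This is a scientific choice. The protocol gives its nine genes as examples, and the other changes stand without it.

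The main changes are to wording and need no extra men or biopsies. The option adds assay work on cores already set aside for RT-PCR. The price is that fewer genes will be called significant. For scale, with 20 per arm and 80% power (two-sided two-sample t test), the detectable difference is 0.91 SD at an unadjusted 0.05, 1.20 SD at 0.05/9 = 0.0056 (first Holm step for nine genes), and 2.14 SD at 0.05/47,000 (Bonferroni). The Benjamini-Hochberg rule is never stricter than Bonferroni at the same level, so its cost on the array lies between the first and last of these.

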**OBJECTIVES**

1. To compare changes in gene expression, following a 12-month intervention of either broccoli or peas in subjects with high-grade PIN.
2. To assess changes in Prostate Specific Antigen (PSA) levels in response to a 12-month intervention of broccoli or peas in the study population.
3. To determine the genotype of individuals for key polymorphic genes and relate them to observed changes in gene expression.

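### The stated array model compares expression levels over all arrays, including pre-intervention ones, so it does not test the between-diet difference in change that Objective 1 asks for

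*Protocol*

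**What the plan says.** The first objective is "To compare changes in gene expression, following a 12-month intervention of either broccoli or peas in subjects with high-grade PIN".

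The Sample Analysis section sets out which six cores per man go on arrays, as follows: "Two from the first sample collection day, two from the second sample collection day and two from the third sample collection day". Each pair takes a left-lobe and a right-lobe core. That is up to six arrays per man. The study design and sampling plan place the first collection before the intervention.

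The Statistical Analysis section then gives the model: "All array data will be analysed using a simple linear model comparing significant differences in gene expression between broccoli and pea treatment groups". It adds one covariate: "Impact of genotype will also be included, combining regression analysis with analysis of group differences". Time appears only in the next sentence: "Pair wise comparisons between time points (baseline, mid and end points) and treatment (broccoli or peas) will be made by dividing by signal intensity", which yields a fold induction per gene. No test is attached to those ratios. The section says that a biostatistician's advice will be sought. It gives control of type I error as its main concern, on arrays carrying more than 47,000 transcripts.

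The groups are formed by matching on genotype and on diet. The protocol does not state randomisation.

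**The concern.** The objective is a difference in differences: change on broccoli minus change on peas. The named model estimates a difference in level between the groups, over arrays from all three visits. These are different quantities. Pre-intervention arrays cannot carry a diet effect, so including them pulls the group coefficient towards zero. They also bring in any difference between the groups that existed before the diet began.

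A second, conditional problem is that arrays from the same man are repeated measures. If the model has no term for the man, its standard error is wrong.

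The trial is a pilot meant to supply inputs for powering later studies. A contrast or variance taken from the wrong model would therefore carry forward into those studies.

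**Working it through.** The plan states no alpha, standard deviation, effect size or power for the arrays, so there is no figure of its own to reproduce.

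**Inputs from the protocol.** Two arrays per man at each of three visits; 20 men per arm; 47,000 transcripts as a lower bound. (The Recruitment Policy also envisages 17 recruited per group, which does not fit 20 completers. The formulas below do not depend on the number of men.)

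**Assumptions, not in the protocol.** Two-sided nominal 5% per transcript. Total variance is 1, split into a man share a, a man-by-visit share b and a core residual e = 1 − a − b. With b = 0, a is the within-man correlation.

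**1. Dilution (needs no correlation assumption).** With equal numbers of arrays per visit, the group coefficient is the mean of the three visit-specific differences.
- Effect d at 6 and 12 months: (0 + d + d)/3 = 2d/3.
- Effect d at 12 months only: (0 + 0 + d)/3 = d/3.
- No diet effect but a stable group difference g from baseline: (g + g + g)/3 = g, whereas the difference in change is g − g = 0.

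A visit main effect alone would not alter these results in balanced data; an arm-by-visit contrast or a baseline adjustment is needed.

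**2. Type I error if the six arrays count as separate observations.** True over assumed variance of the group difference = 6(a + b/3 + e/6), which is 1 + 5a when b = 0. Actual error = 2[1 − Φ(1.96/√ratio)]. For a = 0.5 the ratio is 3.5, 1.96/√3.5 = 1.048, and the error is 0.295.

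**3. The same neglect in an arm-by-time contrast (month 12 minus baseline).** Ratio = 2(b + e/2), which is 1 − a when b = 0. For a = 0.5 the ratio is 0.5, 1.96/√0.5 = 2.772, and the error is 0.006.

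| a (b = 0) | pooled: ratio | pooled: error | simulated | arm by time: ratio | arm by time: error |
|---|---|---|---|---|---|
| 0 | 1.0 | 0.050 | 0.051 | 1.0 | 0.050 |
| 0.1 | 1.5 | 0.110 | 0.111 | 0.9 | 0.039 |
| 0.3 | 2.5 | 0.215 | 0.217 | 0.7 | 0.019 |
| 0.5 | 3.5 | 0.295 | 0.298 | 0.5 | 0.006 |
| 0.7 | 4.5 | 0.356 | 0.358 | 0.3 | 0.0004 |

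Simulations used 20 men per arm and 20,000 replicates per setting. With 10 per arm and a = 0.5, the pooled error was 0.305. The arm-by-time contrast becomes anticonservative only if cores from one visit share enough extra correlation: at a = 0.1, b = 0.4 the ratio is 1.3 and the error 0.086.

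Over 47,000 null transcripts, the expected nominal hits from the pooled comparison are 47,000 × 0.05 = 2,350 at correlation 0. They rise to about 5,150 at 0.1, 10,100 at 0.3 and 13,900 at 0.5.

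**4. If the model is instead fitted at month 12 only.** Dilution disappears, but two lobes per man remain. The ratio is 1 + a when b = 0, giving errors of 0.062, 0.086, 0.110 and 0.133 at a = 0.1, 0.3, 0.5 and 0.7. It is still a comparison of levels without baseline.

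**5. One value per man.** Averaging the lobes, taking each man's month-12 minus baseline change and comparing arms by a two-sample t-test gave simulated errors of 0.048 to 0.051 in every 20 v 20 setting tried, and 0.052 with 10 per arm and a = 0.5.

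**The case against.** The best defence is that the section is a sketch. It does not say that arrays are independent, that lobes are left unaveraged or that no man term will be fitted. A statistical analysis plan, not at hand here, or the promised biostatistical advice could supply all of this. The correlations and the 5% level above come from outside the document. Time is not ignored, because comparisons across visits are planned. RT-PCR is to confirm selected genes.

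Much of this stands, and it rules out several stronger readings.
- A reader might infer that the plan treats six arrays per man as independent. That is an inference from the words simple linear model and the absence of a man term; the text does not say it.
- A reader might infer that error rates are inflated throughout. Inflation applies to the pooled group comparison. For the arm-by-time contrast, ignoring the man is usually conservative and costs power.
- A reader might infer that raw, unpaired ratios will be used. Transcript levels are to be normalised first, and the text does not say whose signals are divided or on what scale.
- A reader might infer that a gene will be called diet-responsive when it changes on broccoli and not on peas. No such rule is stated, so no error rate can be attached to it.

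The defence does not answer the mismatch itself. The protocol does more than leave the model open: it names one, and that model targets a level difference. Advice still to be sought does not change the stated model. RT-PCR uses other cores from the same men, so it cannot separate a diet effect from a difference between the groups at baseline.

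**Conclusion.** The point holds in this form: the only stated inferential model does not estimate the Objective 1 quantity, and the protocol states no between-arm test of change from baseline. Read literally, the group coefficient recovers two thirds of an effect present at both later visits and one third of an effect present only at month 12. This assumes equal numbers of arrays per visit. Six arrays per man is a planned maximum, because RNA quality and the expected 40% drop-out will reduce it. Where a man's later arrays are lost and his baseline arrays are kept, the pre-intervention weight rises. Because allocation is by matching with randomisation not stated, baseline differences in expression can also enter the comparison.

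The type I error of 0.05 to 0.36 is a conditional risk. It rests on the inferred independence of arrays, an assumed 5% level and assumed correlations of 0 to 0.7. It still matters, because any positive correlation would work against the plan's own priority of limiting false positives.

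**What to change.** In the Statistical Analysis section, replace the pooled model with one analysis per transcript on log2 expression:
- Average the two lobes for each man at each visit.
- Compare month-12 expression between arms, adjusted for the man's own baseline, with genotype kept as the plan already includes it. An equivalent choice is a mixed model with man and man-by-visit effects and an arm-by-visit contrast.
- Name that arm contrast as the Objective 1 result.
- Report the fold ratios between time points as description only.

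Because the groups are formed by matching, it is also sensible to show the simple change-score comparison alongside. Adjusting for a noisily measured baseline need not remove a baseline difference completely.

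The cost is revised wording and slightly more analysis work. No new samples or data are needed.
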